### Additional analyses

#### Acceptability analysis

Children’s acceptability will be calculated by the percentage (%) of ‘*yes’* and ‘*no’* responses and the 3-point scale will be calculated as a mean. In line with the children, parent’s acceptability will be calculated by the percentage (%) of ‘*yes’*,* ‘no’ and ‘unsure’* responses. For the 5-point scales, a mean score will be calculated.

#### Qualitative analysis

Content analysis will be used for all open-ended questions (e.g., functionality appreciation and child and parent acceptability).

For functionality appreciation, two checkers (KG and HS) will independently assess children’s responses at each time point (T1, T2 and T3), determining which are valid based on the theoretical framework and conceptualisation of functionality appreciation ([52]). A valid response should fit into one of the six defined domains: (1) bodily senses and sensations (e.g., see, hear, smell), (2) creative endeavours (e.g., drawing), (3) internal processes (e.g., breathing), (4) physical capacities (e.g., playing games, sports), (5) communicating with others (e.g., hugging) and (6) self-care (e.g., brushing teeth), through importantly through the worldview of a child. Duplicate responses (e.g., walk and walking) will be collapsed and counted as one. Invalid responses include simply naming body parts (e.g., legs, arms) or non-sensical responses that do not fit the categories listed above. We will calculate a two-way mixed-effects, single-rate, absolute agreement ICC [65] to indicate if scoring is consistent between raters. A score of at least 0.75 indicates good reliability [65]. A total score for functionality appreciation will be the sum of valid responses, with higher scores indicating higher functionality appreciation.

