### Control content

#### Control 1: ‘BlippiGgoes to the Dentist’ – 15-minute episode

The 15-minute control group will watch a Blippi episode containing no body image or appearance-related messaging. In this episode, Blippi goes to the dentist for a check-up and learns the importance of oral hygiene. This episode was chosen for its comparable length (e.g., 14 min), similar format with the intervention episode, and its alignment with the disclosed study theme in the parent information sheet: evaluating the impact of children’s media on children’s well-being self-esteem.

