#### Control 2: ‘Blippi Brushes his Teeth’ – music video

The music control group will watch a 2 min 29-second Blippi music video containing no body image or appearance-related messaging. This music video is up-beat and features Blippi brushing his teeth. This music video was chosen for similar reasons as above; it featured the same Blippi actor as our intervention music video, was comparable in length and format, and was thematically aligned to the topic of children’s media, well-being, and self-esteem.

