Finally, it was evident the attention span of children this age was short, owing to the increasing despondent responses from the children the longer the activity took (e.g., child would lose interest, hop around, stare at things on the wall, play with the materials, or tell the moderator they were bored). To circumvent this, the decision was made to use two items to assess body appreciation. The item ‘*do you love your body?*’ was selected for being the most readily understood, broad in its messaging (i.e., not directed toward appearance or functionality), and providing the most variability in responses given by the children in our public involvement work. The second item, ‘*how amazing do you think your body is?* was chosen because it directly maps onto the intervention’s key messages. Finally, children responded well to stepping on the small, medium, or large circles to indicate their answer.

Four filler items will also be asked, dispersed amongst the body appreciation items. These will be different at each time-point. Examples include: *‘do you love broccoli?’*, ‘*do you love brushing your teeth?’* and *‘do you love playing outside?’.* The filler items will act as an icebreaker to the activity, and a mechanism to reduce social desirability [61]. Each moderator conducting the interview will praise the child for their participation and engagement, focusing on their involvement and effort rather than a specific response, to avoid influencing their answers.

This measure will be called ‘Circles’ to the participating children.

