#### Functionality appreciation

An adapted version of a measure used by Swami et al. [47] and Dohnt and Tiggemann [45] among a similar age group will be used to measure functionality appreciation. The measure is open-ended and asks children to; *‘tell me all the amazing things you can do with your body’*. In line with Swami et al. [47] and Dohnt and Tiggemann [45] children will be allowed to respond with as many answers as they wish. The moderator will ask the question then will turn over a 60-second sand timer. Children can respond with as many answers as possible before the sand runs out. If a child is still talking when the sand timer had finished, they are allowed to continue until they coame to a natural stop. Responses will be recorded verbatim.

This measure has been refined through several rounds of public involvement with children, teachers, and parents. The wording used by Swami et al. [47] and Dohnt and Tiggemann [45] differed slightly as their questions directly related to the theme of the intervention being tested. For example, Swami et al. [47], who evaluated a theatre production of Cinderella *(‘Cinderella: the AWESOME truth’*) which encouraged children to recognise their own awesome and unique qualities, asked children to list *‘what is unique about you?*’. Dohnt and Tiggemann [45] who evaluated a positive body image storybook focusing on special talents asked children to list ‘*what special talents do you have?*’. Our interventions encourage children to recognise the amazing things their body can do. Therefore, we tested the following item with our public involvement group for comprehension; ‘*tell me as many things as possible that your body can do. You can say things that happen inside your body or things different body parts can do – you can say anything your body does for you!’.* These instructions were evidently too lengthy. Consequently, a simplification of the wording was implemented with the addition of the term ‘amazing’ to qualify responses. An absolute count score will be calculated, with a higher number of responses indicating higher functionality appreciation. In addition, content analysis will be conducted, exploring the content of children’s answers to strengthen the interpretation of our findings.

This measure will be called ‘Time’ to the participating children.

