Immediately following the screening of their allocated media content, children will complete the post-interview (T2), with a moderator. While this is happening, parents will be asked to complete a paper-and-pen questionnaire. Once finished, participants will be thanked for their time and children will receive a small gift (e.g., stickers). Each parent will receive a secure link to their assigned media and will be encouraged to watch it again with their child at home over the next seven to ten days. Snacks and water will be available for children to have before, during, or after the session.

Approximately seven to ten days later, children will attend a follow-up session (T3) accompanied a parent. Children will engage in a follow-up interview with a moderator (i.e., the same format as T1 and T2). Following the completion of this third interview, parents will be provided with a debrief form which will include the explicit study aims, the condition they were allocated in, and details of mental health resources available for parents and children. Finally, to compensate participants for their time, We Are Family will organise thank you incentives. Parents will receive £130 in the form of cash payment, voucher, or donation to a charity of participant’s choice, and children will receive another small gift (e.g., stickers) and a certificate. See the schedule of enrolment, interventions and assessments in Fig. 4. The SPIRIT checklist is presented in Supplementary File 2.

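### Both control films are dental-themed and tooth-brushing counts as a valid functionality answer, so control-film recall may dilute this secondary outcome; prespecify symmetric re-scored analyses

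*Protocol article*

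**What the plan says.** The Control content section describes the two comparators. In the 15-minute control episode, "Blippi goes to the dentist for a check-up and learns the importance of oral hygiene". Of the control song the article says: "This music video is up-beat and features Blippi brushing his teeth". Both were chosen for length, format and fit with the disclosed study theme, and because they carry no messages about body image or appearance.

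Functionality appreciation is a secondary outcome. The child is asked to "tell me all the amazing things you can do with your body", with a 60-second sand timer, and the answers are written down verbatim. Under Qualitative analysis, two checkers decide which answers are valid against six domains. The sixth is given as "6) self-care (e.g., brushing teeth". Then "A total score for functionality appreciation will be the sum of valid responses", and "Duplicate responses (e.g., walk and walking) will be collapsed and counted as one". No stated rule treats answers shown in the child's own film differently.

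On timing, the Procedure section says "Immediately following the screening of their allocated media content, children will complete the post-interview (T2"). In the music arms the neutral 10-minute video comes first, so the song is the last film seen before the interview. Under Repeat watching, families receive a link to their assigned film and are encouraged to view it again before T3.

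**The concern.** The controls were selected to be neutral on appearance, but they are not neutral for this scoring rule. The subject of both films lies next to, or is identical with, an answer that the protocol itself names as valid. A control child who repeats what was just on screen can gain a point without any change in how they value their body's functions.

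Hypothesis H1 predicts a T2 gain in functionality appreciation relative to control, and H7 predicts sustained effects at T3. If control counts rise through film recall, the contrast shrinks, and a null or small result could not be told apart from an ineffective intervention. The Background section already reports an earlier micro-intervention whose control performed as well as the intervention, a result attributed to what the control episode showed. The possibility that control content is not inert is therefore familiar ground for this trial.

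**Working it through.** **Passages side by side**

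- Control episode: dentist check-up and oral hygiene. Control song: tooth-brushing. (Control content)
- Valid answers include self-care, with tooth-brushing as the example. (Qualitative analysis)
- Score: sum of valid answers, duplicates counted once. (Qualitative analysis)
- T2 directly after the film; re-watching before T3. (Procedure; Repeat watching)

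Tooth-brushing itself can therefore add at most one point per child. It adds nothing to the change for a child who already named it at T1.

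**The plan's own figure**

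From Statistical power and sample size: two-sided alpha 0.05, power 90%, d = 0.3, pre-post correlation r = 0.75. With the ANCOVA variance factor,

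n per arm = 2(1 − r²)(z₀.₉₇₅ + z₀.₉₀)² / d² = 2 × 0.4375 × (1.960 + 1.282)² / 0.09 ≈ 102.2, rounded up to 103.

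This reproduces the stated 103. At the intended 105 per arm, power is 90.8%. None of these figures is in dispute.

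**Size of a possible shift**

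Let p be the net share of control children who give one extra valid answer because of the film. The control mean rises by p answers, or p/SD in standardised units. The net effect is d = 0.3 − p/SD if the true effect is 0.3. Power at 105 per arm is Φ(d / √(2(1 − r²)/105) − 1.960), where the square root is 0.0913.

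The article gives neither p nor the SD of the count. Both are assumed here: p from 10% to 30%, SD from 2 to 4. The planning values d = 0.3 and r = 0.75 are carried over to this outcome for illustration only.

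| p | SD | Shift (SD units) | Share of 0.3 | Net d | Power, n = 105 |
|---|---|---|---|---|---|
| 10% | 4 | 0.025 | 8% | 0.275 | 85% |
| 10% | 2 | 0.050 | 17% | 0.250 | 78% |
| 20% | 4 | 0.050 | 17% | 0.250 | 78% |
| 20% | 2 | 0.100 | 33% | 0.200 | 59% |
| 30% | 4 | 0.075 | 25% | 0.225 | 69% |
| 30% | 2 | 0.150 | 50% | 0.150 | 38% |

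The shift runs from about 0.03 to 0.15 SD. The table isolates recall of the control film and sets recall of the intervention film to zero, so it does not estimate net bias.

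**The case against.** The strongest reply is that recall works on both sides. The intervention song names body functions, particularly the senses, which score under domain 1. The intervention episode is about dancing, a natural fit for physical capacities. A rise in those arms may be recall too, and the net effect could favour either side. This stands. It does not remove the concern, because body functions are the message the intervention films are meant to convey, whereas tooth-brushing in the controls is incidental. It does rule out a one-sided remedy. Striking only dental answers from the main score would delete what the controls prompt and keep what the interventions prompt. It would also depart from a framework in which self-care is a defined domain.

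Other limits also stand. A prompted answer may displace another within the timed task. The planned content analysis might reveal a cluster of tooth-brushing answers, though no adjustment of the score is stated. For the episode, the article mentions a check-up and oral hygiene, not tooth-brushing as such.

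A reader might infer that the example filler question "do you love brushing your teeth" prompts the answer a second time in the controls. The article does not support that: fillers go to every arm and differ by time point, so they create no difference between arms.

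**Conclusion.** The overlap between control content and the scoring rule is on the page, and following the plan as written can raise control counts for a reason unrelated to the intended contrast. Taken alone, this pulls functionality appreciation towards no difference at T2, and possibly at T3.

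Its size is uncertain. Under the assumed 10% to 30% of control children and an SD of 2 to 4, the shift is about 0.03 to 0.15 SD, or 8% to 50% of the planning effect. The article cannot narrow that range.

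Two stronger readings are tempting, and neither is supported. One is that the trial's main result is biased; the primary outcome is body appreciation at T2, which does not use this count. The other is that the functionality contrast is certainly biased towards zero overall; the intervention films also prompt scoring answers, so the net direction is open. The point is a cheap improvement to one secondary outcome.

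**What to change.** Keep the planned count as the main score. Prespecify two sensitivity analyses for T2 and T3, scored identically in all four arms and at T1, T2 and T3:

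- (a) a count that excludes tooth-brushing and dental-care answers;
- (b) a count that excludes any answer shown in any of the four films, from a list fixed before coding.

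State that a null or reduced effect on functionality appreciation will be interpreted in light of both. Analysis (a) shows how much the control films may have diluted the contrast, and (b) shows how much of any contrast rests on repeating film content in either direction.

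The cost is small. Answers are already recorded verbatim and assessed by two checkers, so no new data, participants or films are needed. The downside is a little extra coding and the loss of some genuine answers, confined to the sensitivity analyses.

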### Ethical approval and trial registration

This study has received Research Ethical Approval (CHSS.23.09.021) from the College of Health, Science and Society, at the University of the West of England, Bristol. The trial is also registered with Clinical Trial.gov reference number: NCT06146647.

### Data management, data availability and sharing

Each participant will be given a unique participant ID for the purpose of matching responses over time. Anonymous data from participants (children and parents) from each timepoint (T1, T2 and T3) will be collected via paper and pen and entered into SPSS by members of the research team (HS, KG). The data file will be stored on a university approved cloud storage (e.g., OneDrive) and hard copies stored in a locked cabinet in line with the university’s policy. Hard copies will be screened for personal information and anonymised if required. The data file will be screened for data quality including completeness. Digital consent data and personal identifiers (e.g., participant contact details) will be collected by the research agency and kept securely until the end of the project; this information will not be shared with the authors. Audio recordings will be securely uploaded, cross-referenced and deleted once fidelity checks and inter-rater reliability assessments have been completed and resulting paper has been published.

An independent data monitoring committee will not be used as this project is deemed low risk and data collection will take place in a short period (a few weeks). Further, research team members who are not be concealed from condition allocation (i.e., not the statisticians) will review the data as it accumulates to assess for risk. The pilot also allows for a safety assessment of the trial.

The funder and the research agency will not have access to the raw data and all parties have a data processing agreement in place. Anonymised data will be made available upon reasonable requests for non-commercial use. Requests should be made to the project lead and corresponding author (NC).

### Dissemination

Providing there is no evidence of harm, the two interventions will be uploaded to Blippi’s YouTube channel, which has over 22 million subscribers on YouTube (as of December 2024). Therefore, there is huge scope for reaching children around the world in an organic way.

The findings from this study will be disseminated in peer reviewed publications, delivered as presentations at relevant academic conferences, and shared among the social media outlets, podcast episodes and websites.

## Discussion

Micro-interventions offer an innovative approach for targeting young children with positive body image content and may help to mitigate the onset of body image concerns in later childhood. They can be easily embedded into children’s media environments (especially online platforms) thereby disrupting the ubiquitous problematic content that currently permeates these spaces. Directing positive body image content towards children as young as four is potentially a cost-effective preventative strategy for targeting mental health concerns at scale. This study protocol reports on the development and planned randomised controlled trial of two positive body image media micro-interventions among young children aged 4–6 years old. To our knowledge, these are the first interventions designed to promote positive body image among children as young as four, with no published work having explored the medium of music video among this group.

The proposed study has numerous strengths, addressing previous gaps within the literature. Firstly, the proposed randomised controlled trial (RCT) design has been rigorously developed, fully powered, and with the inclusion of active control groups; the gold standard for intervention evaluations [66]. We also include a one-week follow-up period to assess the short-term effectiveness of the micro-interventions and explore any dose response or delayed effects, building upon the preliminary micro-intervention work which has been conducted in field of body image. Secondly, the utilisation of several public involvement groups within the development of the interventions but also the research process only strengthens the rigour of our study. Thirdly, our sample will be gender inclusive, extending the groundwork laid by Dohnt and Tiggemann [45] who were the first to assess a media based positive body image intervention (i.e., storybook) for young children but exclusively among girls. Finally, our recruitment pool will span Birmingham and London, the UK’s two largest cities, both of which diverse in terms of ethnicity and socio-economic status.

Despite several strengths, there are some limitations, mainly related to the challenges of working with very young children. First, scant body image measures were available for administration among 4–6-year-olds. As such, the measures described in this paper were purpose built or were adapted from the few age-appropriate measures available. Although the measures were carefully developed with body image experts, informed by current evidence and several rounds of public involvement feedback, further research beyond the scope of this study will be required to conduct a rigorous validation to examine their psychometric properties. We believe this is an important next step in being able to advance the understanding of young children’s body image.

Similarly, the quality of the self-report data we obtain from this age group may vary. Due to children’s developmental capacity around ages 4 to 6 years, uncertainties persist regarding the amount of unusable data that may be collected (e.g., non-sensical responses, child refusal to engage or interact, or simply a lack of comprehension of the questions). From the beginning of the project, our measures and processes were thoroughly informed by public involvement work to mitigate the likelihood of unusable data. Nevertheless, an awareness that some participant responses may be unusable has been factored into our power calculations. It is hoped that by conducting this work and being transparent in our research endeavours, we can shed light on these issues for other researchers to learn from.

Designing and evaluating interventions through a collaborative process between academics, creatives partners and industry as described in this protocol paper is hugely beneficial for many reasons. All stakeholders bring different skills and expertise, together ensuring interventions are developed to be as acceptable and enjoyable to the target group as possible, while also grounded in a scientific evidence-base. Academic partners bring the scientific knowledge including current evidence on attitudes and behaviour change, as well as rigorous research methods. The creative partners bring the academic messaging to life through storytelling, animation, and humour. Finally, industry partners can maximise intervention reach. If proven to be effective, these stand-alone media micro-interventions have potential to reach hundreds of thousands of young children in many countries across the world.

## Data Availability

No datasets were generated or analysed during the current study.

## Abbreviations

UK: United Kingdom
RCT: Randomised Controlled Trial
T1, T2, T3: Time One, Time Two, Time Three
SES: Socio-economic Status
TV: Television
